## Results

### Overview

The study is a National Institutes of Health–funded R15 (Research Enhancement Award) project supported by the National Library of Medicine. We began collecting data in July 2021 via pilot studies, and here provide some preliminary results and summarize our early observations. The full results and analysis of the study will be shared in future publications when we complete the study.

### Instruments

Based on a literature review, metrics were developed to assess research hypotheses [1,2,4,6-9,39]. Most of the dimensions used to evaluate clinical research hypotheses include clinical and scientific *validity*; *significance* (regarding the target population, cost, and future impact); *novelty* (regarding new knowledge, impact on practice, and new methodology); *clinical relevance* (regarding medical knowledge, clinical practice, and policies); *potential benefits and risks*; *ethicality*; *feasibility* (regarding cost, time, and the scope of the work); *testability*; *clarity* (regarding purpose, focused groups, variables, and their relationships); and *researcher interest level* (ie, willingness to pursue).

Multiple items were used to measure the quality for each dimension mentioned above. For each item, a 5-point Likert scale (1=strongly disagree, 5=strongly agree) was used for measurement. After internal consensus, we conducted external consensus and sought feedback from the external expert panel via an online survey [44]. The metrics are revised continuously by incorporating feedback. The expert panel will use our online survey [45] to evaluate research hypotheses generated by research participants during the study sessions.

We have developed the initial study scripts for Study 1 and have revised them after the pilot study sessions (Study 0). We have developed the screening survey for the recruitment process. The follow-up survey is administered after each study session, regardless of the group. The standard SUS survey [46,47] has been modified to add one more option in order to allow users to elaborate on what caused any dissatisfaction during the usability study.

### Recruitment

Currently, we are recruiting all levels of participants, including inexperienced clinical researchers, experienced clinical researchers, and a panel of clinical research experts. Recruitment began in July 2021 with pilot study participants. To participate, anyone involved in clinical research can share their contact email address by filling out the screening survey [48]. So far, we have completed 16 study sessions with inexperienced clinical researchers who have either used or not used VIADS in Study 1.

### Study 1

For this study, we are using data from the National Ambulatory Medical Care Survey (NAMCS) conducted by the Centers for Disease Control and Prevention [36]. The NAMCS is a publicly accessible data set of survey results related to clinical encounters in ambulatory settings. We processed raw NAMCS data (ICD9 codes and accumulated frequencies) from 2005 and 2015 to prepare the needed data sets for VIADS based on our requirements.

The experience level of the clinical researchers was determined by predetermined criteria. To determine which group a participant joins (inexperienced [groups 2 and 4] or experienced [groups 1 and 3] clinical researchers), we used the R statistical software package (blockrand [49]) to implement block randomization. The random blocks range from 2 to 6 participants.

### Initial Observations

We have noticed that both forward [27] and backward reasoning had been used by participants during the study sessions. In addition, some participants did not start from data or a hypothesis. Instead, the reasoning started from the participant’s focused (and often familiar) area of knowledge related to several ICD9 codes in the focus area being examined. The research hypotheses were then developed after examining the data on the focused area.

Many participants did not use any advanced analysis during the study sessions. However, they did use their prior experience and knowledge to generate research hypotheses based on the frequency rank of the provided data sets and by comparing the 2 years of data (ie, 2005 vs 2015).

Noticeably, VIADS can answer more complicated questions both systematically and more rapidly. However, we noticed that the training session required to enable use of VIADS increased participants’ cognitive load. Cognitive load refers to the amount of working memory resources required during the task of thinking and reasoning. Without a comprehensive analysis, we cannot yet draw further conclusions about the potential effects of this cognitive load.

## Discussion

### Significance of the Study

A critical first step in the life cycle of any scientific research study is formulating a valid and significant research question, which can usually be divided into several scientific hypotheses. This process is often challenging and time-consuming [1,3,38,50]. Currently, there is limited practical guidance regarding generating research questions [38] beyond emphasizing that it requires long-term experience, observation, discussion, and exploration of the literature. A scientific hypothesis–generation process will eventually help to formulate relevant research questions. Our study aims to decipher the process of scientific hypothesis generation and determine whether a secondary data analytics tool can facilitate the process in a clinical research context. When combined with clinical researchers’ experiences and observations, such tools can be anticipated to facilitate scientific hypothesis generation. This facilitation will improve the efficiency and accuracy of scientific hypothesis testing, formulating research questions, and conducting clinical research in general. We also anticipate that an explicit description of the scientific hypothesis–generation process with secondary data analysis may provide more feasible guidance for clinical research design newcomers (eg, medical students and new clinical investigators). However, we have not completed all study sessions, so we cannot yet analyze the collected data in order to draw meaningful conclusions.

### Interpretation of the Study and Results

Participants have been observed to use analogical reasoning [51] both consciously and subconsciously; meanwhile, some participants verbally expressed that they avoided analogical reasoning intentionally to be more creative during the study sessions. The participants intentionally did not use the same pattern of statements for all the topics supported by the data sets. The way we organized the data sets seems to promote the participants to think systematically when using the data sets. For instance, the use frequencies of ICD9 codes were sorted from high to low in each data set. However, what would constitute the perfect balance between systematic structure and randomness during scientific hypothesis generation is unknown. Intuitively, both systematic reviews and random connections should be critical in generating novel ideas in general, regardless of academic settings or industrial environments. Concrete evidence is needed to draw any conclusions about the relationships between the 2 during scientific hypothesis generation with certainty. Additionally, the current version of VIADS can only accept coded data using ICD9-CM, ICD10-CM, and MeSH. This inevitably limits the types of hypotheses VIADS can generate. We also recognize that other more broadly used hierarchical terminologies, such as SNOMED CT, RxNorm, and LOINC, could provide additional valuable information related to more comprehensive aspects of clinical care. However, our current version of VIADS cannot use such information at this time.

Analyzing the research hypothesis–generation process may include several initial cognitive components. These components can consist of searching for, obtaining, compiling, and processing evidence; seeking help to analyze data; developing inferences using obtained evidence and prior knowledge; searching for external evidence, including literature or prior notes; seeking connections between evidence and problems; considering feasibility, testability, ethicality, and clarity; drawing conclusions; formulating draft research hypotheses; and polishing draft research hypotheses [1-3,8,39,52]. These initial components will be used to code the recorded think-aloud sessions to compare differences among groups.

We recognize that research hypothesis generation and the long refining and improving process matter most during the study sessions. Without technologies to capture what occurs cognitively during the research hypothesis–generation process, we may not be able to answer fundamental questions regarding the mechanisms of scientific hypothesis generation.

Establishing the evaluation metrics to assess research hypotheses is the first step and the critical foundation of the overall study. The evaluation metrics used will determine the quality measurements of the research hypotheses generated by study participants during the study sessions.

Research hypothesis evaluation is subjective, but metrics can help standardize the process to some extent. Although the metrics may not guarantee a precise or perfectly objective evaluation of each research hypothesis, such metrics provide a consistent instrument for this highly sophisticated cognitive process. We anticipate that a consistent instrument will help to standardize the expert panel’s evaluations. Additionally, objective measures, such as the number of research hypotheses generated by the study participants and the average time each participant spends generating each research hypothesis, will be used in the study. The expert panel is therefore expected to provide more consistent research hypothesis evaluations with the combined metrics and objective measures.

Although developing metrics appears linear, as presented in Figure 2, the process itself is highly iterative. No revision occurs only once, and when we reflect on the first 3 stages of development, one observes that major revisions during the first 3 stages involve separating questions in the survey and refining the options for the questions. These steps reduce ambiguity.

### Challenges

Many challenges have been encountered while conducting the research hypothesis–generation study sessions. These include the following:

What can be considered a research hypothesis? What will not be considered a research hypothesis? The response will determine which research hypotheses will be evaluated by the panel of clinical research experts.How should the research hypothesis be measured accurately? Although we developed workable metrics, the metrics are not yet perfect.How can we accurately capture thinking, reasoning, and networking processes during the research hypothesis–generation process? Currently, we use the think-aloud method. Although think-aloud protocols can capture valuable information about the thinking process, we recognize that not all processes can be articulated during the experiments, and not everyone can articulate their processes accurately or effectively.What happens when a clinical researcher examines and analyzes a data set and generates a research hypothesis subconsciously?How can we capture the roles of the external environment, internal cognitive capacity, existing knowledge base of the participant, and interactions between the individual and the external world in these dynamic processes?

When faced with challenges, we see opportunities for researchers to further explore and identify a clearer picture of research hypothesis generation in clinical research. We believe that the most pressing target is developing new technologies in order to capture what clinical researchers do and think when generating research hypotheses from a data set. Such technologies can promote breakthroughs in cognition, psychology, computer science, artificial intelligence, neurology, and clinical research in general. In clinical research, such technologies can help empower clinical researchers to conduct their tasks more efficiently and effectively.

### Lessons Learned

We learned some important lessons while designing and conducting this study. The first lesson involved balancing the study design (straightforward or complicated) and conducting the study (feasibility). During the design stage, we were concerned that the 2×2 study design was too simple, even though we know it does not negatively impact the value of the research. We simply considered experience levels and whether the participants used VIADS in a very complicated cognitive process. However, even for such a straightforward design, only 1 experienced clinical researcher has volunteered so far. Thus, we will first focus on inexperienced clinical researchers. Even for study sessions involving inexperienced clinical researchers, considerable time is needed to determine strategies for coding and analyzing the raw data. In order to design a complicated experiment that answers more complex questions, we must consider balancing practical workload, recruitment reality, expected timeline, and researchers’ desire to pursue a complex research question.

Recruitment is always challenging. Many of our panel invitations to clinical research experts either received no response or were rejected, which significantly delayed the study timeline, in addition to the effects of the COVID-19 pandemic. Furthermore, the IRB approval process was time-consuming, delaying our study when we needed to revise study documents. Therefore, the study timeline includes the IRB initial review and rereview cycles.

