### Study Design

Study 1 tests all 3 study hypotheses. If the study hypotheses are supported in Study 1, we will conduct a follow-up study (Study 2) to examine whether and how the efficiency or quality of research hypothesis generation may be improved or refined.

We will use the think-aloud method to conduct the following tasks: (1) observe the research hypothesis–generation process; (2) transcribe data, and analyze and assess if VIADS [22] and different levels of experience of clinical researchers influence the process; and (3) assess the interactions between VIADS (as an example of a secondary analytical tool) and the experience levels of the participants during the process. Figure 3 summarizes the Study 1 and Study 2 procedures.

#### Study 1

Experienced and inexperienced clinical researchers conduct research hypothesis–generation tasks using the same secondary data sets. The tasks are captured to describe participants’ research hypothesis–generation processes when guided by analysis of the same data sets. VIADS is also used as an example of a secondary data analytics tool to assess participants’ research hypothesis–generation processes. Accordingly, 2 control groups do not use VIADS, while 2 intervention groups do use it.

A pilot study, Study 0, was conducted in July and August 2021 for each group to assess the feasibility of using the task flow, data sets, screen capture, audio and video recordings, and study scripts. In Study 1, 4 groups are utilized. Table 3 summarizes the study design and participants in each group. The 4 groups will be compared in order to detect the primary effects of the 2 factors and their interactions after completing Study 1. After recruitment, the participants are separated into experienced or inexperienced groups based on predetermined criteria. Then, the participants are randomly assigned to a group that uses VIADS (3-hour session, with 1 hour to conduct VIADS training) or does not use VIADS (2-hour session) via block randomization.

**Table 3 table3:** Design of Study 1 for assessment of the hypothesis–generation process in clinical research.

Variable	Number of experienced clinical researchers	Number of inexperienced clinical researchers
Not using VIADS	8 (Group 1)	8 (Group 2)
Using VIADS	8 (Group 3)	8 (Group 4)

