### Data and Statistical Analysis

While conducting the given tasks, the qualitative data collected via the think-aloud method will be transcribed, coded, and analyzed according to the grounded theory [41,42], a classical qualitative data analysis method. This data analysis has not begun yet because data are still being collected. Combined analysis of discourse [30], video recordings of the study sessions, and screen activities will be conducted. The main components or patterns that we will focus on during analysis include potential nonverbal steps, sequential ordering among different components (such as prioritization of the use of either experience or data) across groups, seeking and processing evidence, analyzing data, generating inferences, making connections, formulating a hypothesis, searching for information needed to generate research hypotheses, and so forth. Ideally, based on video analyses and observations, we plan to develop a framework for the scientific hypothesis–generation process in clinical research, which is guided by secondary data analytics. Similar frameworks exist in education and learning areas [43], but do not currently exist in the field of clinical research.

The outcome variable used is based on the participants’ performance in research hypothesis–generation tasks. The performance is measured by the quality (eg, significance and validity) and quantity of the research hypotheses generated through the tasks and the average time to generate 1 research hypothesis. At least three clinical research experts will assess each hypothesis using the scientific hypothesis assessment metrics that were developed for this study. The metrics include multiple items, each on a 5-point Likert scale. The details of the metrics are described in the Instrument Development section.

The data will be analyzed with a 2-tailed factorial analysis. We calculated the required sample size in G*Power 3.1.9.7 for a 2-way ANOVA. The sample size was 32 based on a confidence level of 95% (α=.05), effect size f=0.5, and power level of 0.8 (β=.20).

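### Near-sequential accrual leaves the non-randomised experience contrast almost aliased with calendar period, so pool the expert rating, word the effect as association, and qualify the power figure

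*Protocol article*

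**What the plan says.** Study Design (Table 3) plans four cells of 8. Participants are first sorted into experience strata by preset criteria and then randomised to VIADS or no VIADS. The stated aim includes assessing whether VIADS and "different levels of experience of clinical researchers influence the process"; the Introduction frames the study in the same causal terms.

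On accrual, the Recruitment section reports: "So far, we have completed 16 study sessions with inexperienced clinical researchers". Lessons Learned adds that "only 1 experienced clinical researcher has volunteered so far" and continues: "Thus, we will first focus on inexperienced clinical researchers". Recruitment also states that all participant levels are currently being recruited.

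On analysis, the Data and Statistical Analysis section names a 2-way ANOVA of the expert evaluation score with VIADS, experience and their interaction as terms. Its sample size statement reads: "The sample size was 32 based on a confidence level of 95% (α=.05), effect size f=0.5, and power level of 0.8 (β=.20").

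On the outcome instrument, the Instruments section says: "The metrics are revised continuously by incorporating feedback". Challenges lists as an open question what counts as a research hypothesis, and notes that the answer decides which hypotheses the experts will rate.

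The Study 2 section makes that study conditional on Study 1 showing differences by experience and by VIADS use, with alternative paths when either difference is not significant.

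**The concern.** Experience cannot be randomised, so the contrast is observational from the start. The accrual pattern adds a second problem. If nearly all experienced sessions follow nearly all inexperienced ones, anything that changes between the two periods is absorbed into the experience term, and the ANOVA as described has no term for time.

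The most concrete route by which this could matter is the rating. The outcome is an expert score, the instrument is still being revised, and the rule for which statements are rated is unsettled. If the inexperienced hypotheses were rated as one batch and the experienced ones later, any change in instrument, eligibility rule or rater severity would be added to the experience effect.

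Two conclusions are at stake: study hypothesis 1, and the part of the Study 2 decision that turns on the experience contrast. Separately, the planning calculation rests on 32 participants in four full cells. The article reports that the experienced half is almost empty but leaves that figure unqualified.

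**Working it through.** **Inputs from the article.** α = 0.05 two-sided, f = 0.5, target power 0.80, N = 32, 8 per cell (Data and Statistical Analysis; Table 3). Completed: 16 inexperienced. Experienced volunteers: 1 of 8 + 8 = 16 planned.

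**Inputs assumed.** Between-period shift s of 0.1 to 0.5 within-cell SD (the article gives no value); no dropout; an 8 v 8 split of the 16 completed sessions (the article does not give the split).

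**1. The plan's own figure.** For a two-level main effect in a 2×2 design, numerator df = 1, denominator df = 32 − 4 = 28, and λ = f²N = 0.25 × 32 = 8. The critical F is 4.196 and power is 0.779. The smallest N reaching 0.80 is 34 (power 0.805). A normal approximation for a 1-SD difference (f = 0.5 with two equal groups) gives 16 per level, so 32, with power 0.807. The stated 32 is reproduced to within rounding of method; by noncentral F its power is 0.78.

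**2. How close the aliasing is.**
- Strictly 16 inexperienced then 16 experienced: a design with intercept, experience and a two-level period has rank 2 with 3 columns, so the two effects cannot be separated.
- One experienced session in the early period: the correlation between experience and period is 0.94, so the variance inflation factor is 1/(1 − 0.94²), which is 8.5 unrounded. Power for a 1-SD experience effect adjusted for period is then about 0.15.

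Adding a period term later would therefore not rescue the contrast.

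**3. What an assumed shift would do.** With no true experience effect, a shift of s SD acts as f = s/2, so λ = (s/2)² × 32 = 8s².

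| Assumed shift s (SD) | λ | P(significant experience effect) |
|---|---|---|
| 0 | 0 | 0.05 |
| 0.1 | 0.08 | 0.06 |
| 0.25 | 0.50 | 0.10 |
| 0.5 | 2.00 | 0.28 |

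**4. What a shortfall would do.** For experience with 16 inexperienced and m experienced, λ = d² × 16m/(16 + m) and denominator df = 12 + m. At d = 1:

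| m | λ | Power |
|---|---|---|
| 4 | 3.20 | 0.39 |
| 8 | 5.33 | 0.59 |
| 12 | 6.86 | 0.71 |
| 16 | 8.00 | 0.78 |

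With the inexperienced stratum alone, VIADS is tested 8 v 8: λ = d² × (8 × 8)/16 = 4d², denominator df = 14, critical F = 4.600. Power is 0.46 at d = 1 (λ = 4) and 0.80 at d = 1.5 (λ = 9). Experience and the interaction cannot be estimated.

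**5. What is not affected.** VIADS is randomised within stratum, so both of its arms share the same period and accrual order does not bias that contrast. The interaction is the difference between two such contrasts and is disturbed only if the VIADS effect itself changes over time.

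**The case against.** A reader might infer that experienced recruitment starts only once the inexperienced sessions are over. The article does not say so: recruitment is open at all levels and one experienced researcher has come forward. The sequence comes from slow accrual plus a stated priority, so the aliasing is near-complete rather than total.

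A reader might also infer that scripts, tool, data sets and observer all drift between strata. The article largely guards against this. Scripts were revised after the pilot and no later revision is described; VIADS is revised only after Study 1; all groups receive the same data sets; one researcher observes every session. The metric is not used by participants during sessions, so revising it while sessions run does no harm in itself. It matters only if the strata are rated in separate batches, which the article neither plans nor rules out.

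Nor does the article claim 0.80 power under present accrual. It gives one planning calculation and openly reports the recruitment problem. Near-aliasing is a matter of bias and does not lower the nominal power of an unadjusted 16 v 16 test.

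Finally, detailed rules for incomplete accrual commonly sit in a fuller document, and study hypothesis 1 is itself worded as a difference. Both are fair points. What remains is that the aims use causal wording for a non-randomised factor now almost tied to period, that the rating process leaves an avoidable opening for drift, and that the power figure stands beside a reported shortfall without qualification.

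**Conclusion.** The point holds as a cheap improvement. Study 1 can support a statement that experience is associated with hypothesis quality; it cannot support a causal one, and near-sequential accrual makes even the association vulnerable to period effects. No drift has been shown. The probabilities of 0.06, 0.10 and 0.28 describe assumed shifts of 0.1, 0.25 and 0.5 SD, and the shared data sets, scripts and observer argue for the lower end unless rating is done in batches.

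The planned power (0.80 as stated, 0.78 by noncentral F) applies only if all four cells fill. With the inexperienced stratum alone, and assuming an 8 v 8 split, the VIADS test has power of about 0.46 at 1 SD and needs about 1.5 SD for 0.80. Study hypotheses 1 and 3 would then be untested, which is different from the non-significant result that the Study 2 rules address.

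**What to change.** 1. Finalise one version of the metric and one rule for what counts as a research hypothesis before any rating starts. Have the experts rate hypotheses from all groups together, in random order, without knowing the group.
2. Describe the experience effect as an association in the aims and conclusions. Keep causal wording for the randomised VIADS comparison.
3. Record session dates, so that the overlap between strata can be reported.
4. State that N = 32 with power 0.80 (0.78 by noncentral F) is conditional on all cells filling. State now that, if only the inexperienced stratum is available, the test is VIADS v no VIADS within it, with power of about 0.46 at 1 SD and about 0.80 at 1.5 SD if split 8 v 8; that study hypotheses 1 and 3 are reported as not tested; and that the Study 2 rule based on experience is not triggered.

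Cost: rating waits until recruitment closes, and the stated power looks less favourable. The rest is wording and record keeping. Pooled rating has to be settled before rating begins, since it cannot be restored afterwards.
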